#### Level 4 of diagnostic certainty

Newborn infant 'weight' assessed on day 1 or 2 of life (first 48 h of life)

AND

Proxy measure of birth weight used

AND

Weight CATEGORY assessed as <2500 g

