### Level 2B

Uncertain LMP with 2nd trimester scan (14 0/7 weeks to 27 6/7 weeks).

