### Level 2 of diagnostic certainty

1. Woman confirmed as pregnant by cessation of menstrual period and gravid uterus

AND

2. Date (at least month and year) of immunization of pregnant woman recorded in medical records by health care worker who administered/witnessed administration of vaccine

AND

3. Details of disease against which vaccinated

Level 3 of diagnostic certainty

1. Woman/medical attendant reports pregnancy AND

2. Woman reports receipt of vaccination during pregnancy, but no formal recording of immunization available.

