## Annex V. CRFs

### General information

|          |                                                                                                |                                                                                                                                                     |
|----------|------------------------------------------------------------------------------------------------|-----------------------------------------------------------------------------------------------------------------------------------------------------|
|          | DEMOGRAPHICS                                                                            |                                                                                                                                                     |
| 1        | Date of birth                                                                                  |                                                                                                                                                     |
| A | Status of live/stillborn                                                                |                                                                                                                                                     |
| 1        | Sex                                                                                            | Male
Female
Indeterminate
Unknown                                                                                                          |
| 2        | Gestational age                                                                                | .... Weeks .... Day                                                                                                                                 |
| 3 a      | Birth weight units                                                                             | Grams
Kilograms
Pounds
Unknown                                                                                                             |
| 3a       | Birth weight                                                                                   | Please enter a number or enter 0 if unknown                                                                                                  |

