|                                         |                                                                                                                                                                 | Female
Unknown                                                                                                                                                                                                                                                     |
| 3                                       | Please see Reference CRF GA                                                                                                                                     |                                                                                                                                                                                                                                                                       |
| PART 2 - Congenital microcephaly |                                                                                                                                                                 |                                                                                                                                                                                                                                                                       |
| 1                                       | Was the head circumference measured and recorded?
If 'no' or 'unknown' skip question 5.                                                               | Yes
No
Unknown                                                                                                                                                                                                                                                  |
| 2a                                      | What was the head circumference?                                                                                                                                | Please enter a number.                                                                                                                                                                                                                                         |

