| B Last menstrual period (LMP) of the pregnant woman                                                                                                                                                                                                    |                                                                                                                                                                                  |                                                                            |
| 3a                                                                                                                                                                                                                                                            | What is the date of LMP ?
(if ' unknown ', skip to section C)                                                                                                          | Please enter DDMMYYYY or unknown.                                   |
| C Assisted reproduction technology                                                                                                                                                                                                                     |                                                                                                                                                                                  |                                                                            |
| 4                                                                                                                                                                                                                                                             | Was the conception natural (i.e. no assisted reproduction technology was used)?
(if ' yes ' or ' unknown ', skip to section D)                                  | Yes
No
Unknown                                                       |

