### Reference CRF: birth weight

| QUESTION                     |                              | ANSWERS                                  |
|------------------------------|------------------------------|------------------------------------------|
| PART 1 – BIRTH WEIGHT |                              |                                          |
| A                     | Birth                 |                                          |
| 1                            | Date of birth of the newborn | Please enter DDMMYYYY or unknown. |
| B                     | Weight                |                                          |

|              |                                                                                       |                                                                                                    |
|--------------|---------------------------------------------------------------------------------------|----------------------------------------------------------------------------------------------------|
| 1            | Was the newborn weighed?
If 'no' or 'unknown' skip to B4..                  | Yes
No
Unknown                                                                               |
| 2a           | What was the weight of the newborn infant?
If 'unknown' skip to question 3. | Please enter a number.                                                                      |
| 2b           | What are the units of the weight measurement?                                         | Grams
Kilograms
Pounds
Other, please specify
Unknown                                   |
| 3            | Was the weight category assessed as <2500g?                                           | Yes
No
Unknown                                                                               |
| 4            | Was a proxy measure of birth weight used?                                             | Yes, please specify
No
Unknown                                                               |
| 5            | When was the newborn infant weighed?                                                  | Within 24 hours of birth
On day 1 or 2 of life (first 48 hours)
On day 3 or after
Unknown |

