| Fill in the questions below for each dose administered during pregnancy                   |                                                                                                                                                                                    |                                          |

|                                                                          |                                                                                                                      |                                                                                                                                           |
|--------------------------------------------------------------------------|----------------------------------------------------------------------------------------------------------------------|-------------------------------------------------------------------------------------------------------------------------------------------|
| Dose during pregnancy                                      |                                                                                                                      |                                                                                                                                           |
| 4                                                                        | Against which disease was the mother immunized?                                                                      | Tetanus
Influenza
Pertussis
Other, please specify                                                                                |
| 5                                                                        | Was vaccination status obtained from medical records or reported by the mother?                                      | Medical records (e.g. ANC card, vaccination card, vaccine registry, etc.)
Reported by mother but no formal recording
Unknown        |
| 6                                                                        | What is the date of immunization of the pregnant woman?                                                              | Please enter DDMMYYYY or unknown.                                                                                                  |

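### Several Annex V forms do not collect, or skip past, items that the Annex III certainty levels need; this mainly distorts the level distribution and hardly touches the primary applicability proportion

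*Protocol*

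**What the plan says.** Protocol 4.10 classifies identified cases and exposures by GAIA level with an automated tool, and 8.2 builds the data capture system on the Annex V forms. In 5.2.2.1 the primary applicability denominator is every identified case with a completed form. Section 5.3.1 reports the proportion at each level, stratified by site, country, region and facility level. Section 5.4.2 asks what kept Level 3 or 4 cases from reaching Level 1 or 2.

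The relevant form items and level criteria are:

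- **(a) LMP.** The only LMP item on the gestational-age form is "What is the date of LMP", answered by a date or unknown. Preterm birth Level 2B in Annex III reads "Uncertain LMP with 2nd trimester scan (14 0/7 weeks to 27 6/7 weeks"; the same scan with a certain LMP is Level 2A.
- **(b) Birth weight.** If the newborn was not weighed, item B1 says "If 'no' or 'unknown' skip to B4", which passes over B3 (weight category below 2500 g). Low birth weight Level 4 requires "Weight CATEGORY assessed as <2500 g".
- **(c) Assisted conception.** A no or unknown to intrauterine insemination (IUI, item 5a) goes to section D, past the embryo-transfer items 6a and 6b.
- **(d) Microcephaly.** If head circumference was not recorded, the form says "If 'no' or 'unknown' skip question 5". Items 5a to 5d are the ICD-code items.
- **(e) Vaccination date.** Maternal immunization Level 2 accepts "Date (at least month and year) of immunization of pregnant woman recorded in medical records". The form item "What is the date of immunization of the pregnant woman" takes a full day-month-year date or unknown.

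**The concern.** The study measures whether the GAIA levels can be reached with the data that sites hold. If a form does not ask for a criterion, or routes past it, the result reflects the form and not the site's records. An analysis plan can repair a coding rule, but it cannot recover an answer that was never requested. At stake are the level proportions in 5.3.1, the missing-element tables in 5.4 and, for a few routes, whether a case counts as classified in 5.2.2.

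**Working it through.** **The plan's own yardstick.** Table 1 gives 97 cases for an applicability of 50% within 10 points: 1.96² × 0.5 × 0.5 / 0.10² = 96.04, rounded up to 97. This reproduces. No stated figure is in dispute; it only shows what size of distortion would matter.

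**(a) LMP certainty.** Take the preterm-birth levels in Annex III and assume the LMP date is known. Seven other elements may be present or absent: scans in the first, second and third trimester, first-trimester physical examination, fundal height, birth weight and newborn assessment. That gives 2⁷ = 128 patterns. Assign the level to each pattern twice, once with a certain and once with an uncertain LMP.

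| Level if certain / if uncertain | All 128 patterns | 64 patterns with birth weight |
|---|---|---|
| 1 / 1 (first-trimester scan) | 64 | 32 |
| 2A / 2B | 32 | 16 |
| 2A / 3A | 16 | 8 |
| 3A / 3B | 13 | 8 |
| Classified under one only | 2 | 0 |
| Unclassified under both | 1 | 0 |

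- The level depends on the uncollected answer in 32 + 16 + 13 + 2 = 63 of 128 patterns.
- With birth weight recorded and no first-trimester scan, it does so in 16 + 8 + 8 = 32 of 32, and none becomes unclassified.
- Of the 63, 32 + 13 = 45 are splits within Level 2 or within Level 3, 16 cross from Level 2 to Level 3, and 2 change whether the case is classified.
- Ending the questionnaire after a usable first- or second-trimester scan loses no preterm level in any pattern.

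These are counts of patterns, not of infants. SGA uses the same certain/uncertain split for gestational age but adds weighing conditions. Microcephaly Levels 1 and 2A call for a certain LMP with a scan (or an IUI or embryo-transfer date), and Level 2B for an uncertain LMP with a second-trimester scan, so that split is also undetermined.

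**(b) Low birth weight Level 4.** The level needs both a proxy measure (B4) and the category (B3). An unweighed infant is asked B4 but not B3, so the level cannot be met. The other low birth weight levels require a weighing, so the case stays in the denominator as unclassified. If a share f of cases is lost this way, a true applicability A reads A(1 − f). With A = 80% (assumed):

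- f = 2% gives 78.4%.
- f = 5% gives 76%.
- f = 10% gives 72%.

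For comparison, the half-width at 100 cases is 1.96 × √(0.8 × 0.2 / 100) = 7.8 points. The protocol gives no value for f.

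**(c) Embryo transfer.** For preterm birth and SGA, a transfer date counts only together with a first-trimester scan, and that scan alone already gives the gestational-age part of Level 1. The effect there is nil. Only microcephaly Levels 1 and 2A in assisted conceptions can be affected.

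**(d) ICD items.** Read literally, the rule removes the items needed for microcephaly Level 3B and for the coded route to Level 4. Item 6 (physical inspection) keeps the other route to Level 4 open.

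**(e) Vaccination date.** A record with month and year only must be entered as unknown. Level 3 is for women with no formal record, so such a record does not strictly fit there either. Item 8 separately asks whether the date was recorded by the health worker, and can be answered yes.

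**The case against.** **The LMP item may exist.** The item is numbered 3a with no 3b, its skip rule has nothing left to skip, and the footnote to certain LMP is not in the text. A row may have been lost in reading the PDF. This cannot be excluded, and one look at the live eCRF settles it. The rest of that table is intact, and the maternal immunization form also asks only for the date.

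**The primary outcome is hardly affected by (a).** This stands. Section 4.10 speaks of Levels 1 to 3 and 4 to 5, and most affected patterns stay within one numbered level.

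**The other faults are small.** Section 4.7.2 defines low birth weight by a recorded weight, so unweighed infants are a marginal group; but 4.8 also allows identification from registries and ICD codes, so the group need not be empty. The rule in (d) is probably a slip for skipping *to* question 5, since otherwise an unmeasured head would still be asked its circumference, units and timing. Item 8 partly covers (e).

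**A reader might infer that sites would be blamed for form faults.** The documents do not support that as a general claim. An item that nobody was asked would show as missing at every site in the 5.4 tables.

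**A reader might also infer inflated low birth weight or SGA rates.** The General information form says "Please enter a number or enter 0 if unknown", 5.2.1.1 derives low birth weight from recorded birth weight, and 5.5 analyses data as recorded. If a share u of weights were zeros read as grams, a true rate p would appear as (1 − u)p + u; with assumed p = 15% and u = 5% that is 0.95 × 0.15 + 0.05 = 19.3%. But the documents do not show that this field feeds the 5.2.1.1 rates: the form has no head-circumference field and no field for the presence of each outcome, both of which the delivery register in 4.6 records. Zero is a declared code for unknown, 5.5 tabulates missing data, and 8.1 plans range checks. No inflation and no false cases are shown.

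**Conclusion.** The point holds as a set of form faults of unequal weight.

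- **Main fault, (a):** preterm-birth and SGA sublevels, some Level 2 versus Level 3 assignments, and microcephaly Levels 1/2A versus 2B cannot be assigned from the form. For preterm birth this concerns infants without a first-trimester scan. It damages 5.3.1 and 5.4.2 and leaves the primary proportion nearly intact.
- **Primary proportion, (b):** Level 4 is unreachable for unweighed infants, who count as unclassified. The group is probably small.
- **Minor, (c) to (e):** (c) concerns microcephaly in assisted conceptions only, (d) depends on a literal reading, and (e) is partly mitigated by item 8.

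This rests on the forms as printed being the forms in use, and on no unstated rule equating a recorded LMP date with a certain one. The number of affected infants is unknown; f above is an assumption. It should be corrected, but it does not undermine the study.

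**What to change.** 1. Add to the gestational-age form: Is the LMP date certain? (yes, no, unknown). Where the source record is silent, unknown is then a genuine finding about the record.
2. For forms already closed, query this item. Where it cannot be recovered, report 2A/2B and 3A/3B merged, and report 2A/3A and the affected microcephaly levels as undetermined.
3. Route birth-weight item B1 (no or unknown) to B3.
4. Route IUI no or unknown to item 6a.
5. Reword the head-circumference rule so that it skips to question 5.
6. Let the vaccination date be entered as month and year.
7. As a safeguard only, replace the zero code for unknown birth weight with an explicit unknown code, and set any zeros to missing before deriving low birth weight or SGA.

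The cost is a small eCRF update, a note to sites and a round of queries on LMP certainty. The sponsor should decide whether 8.8 treats it as an amendment needing ethics submission.

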### Reference CRF: birth weight

| QUESTION                     |                              | ANSWERS                                  |
|------------------------------|------------------------------|------------------------------------------|
| PART 1 – BIRTH WEIGHT |                              |                                          |
| A                     | Birth                 |                                          |
| 1                            | Date of birth of the newborn | Please enter DDMMYYYY or unknown. |
| B                     | Weight                |                                          |

|              |                                                                                       |                                                                                                    |
|--------------|---------------------------------------------------------------------------------------|----------------------------------------------------------------------------------------------------|
| 1            | Was the newborn weighed?
If 'no' or 'unknown' skip to B4..                  | Yes
No
Unknown                                                                               |
| 2a           | What was the weight of the newborn infant?
If 'unknown' skip to question 3. | Please enter a number.                                                                      |
| 2b           | What are the units of the weight measurement?                                         | Grams
Kilograms
Pounds
Other, please specify
Unknown                                   |
| 3            | Was the weight category assessed as <2500g?                                           | Yes
No
Unknown                                                                               |
| 4            | Was a proxy measure of birth weight used?                                             | Yes, please specify
No
Unknown                                                               |
| 5            | When was the newborn infant weighed?                                                  | Within 24 hours of birth
On day 1 or 2 of life (first 48 hours)
On day 3 or after
Unknown |
| Scale |                                                                                       |                                                                                                    |
| 1            | What type of scale was used?                                                          | Electronic scale
Spring scale
Dial
Color-coded
Unknown                                 |
| 2            | How is the scale graduated?                                                           | To 10 grams
To at least 50 grams
Other
Unknown                                            |
| 3            | How often is the scale calibrated?                                                    | At least once a year
At least once a year, or more often if moved
Other
Unknown           |
| 4            | What is the scale tared to?                                                           | 0 grams
0.00 kg
Other
Unknown                                                             |
| 5            | (For electronic scales): Is the scale placed on a level, hard surface?                | Yes
No
Unknown                                                                               |

|                                                                           |                                                                                                                                                                                                                                                                       |                      |
|---------------------------------------------------------------------------|-----------------------------------------------------------------------------------------------------------------------------------------------------------------------------------------------------------------------------------------------------------------------|----------------------|
| 6                                                                         | Is the infant weighed by measuring the difference between an adult holding the infant and the adult being weighed alone?                                                                                                                                              | Yes
No
Unknown |
| Standard operating procedures (to be completed only once per site) |                                                                                                                                                                                                                                                                       |                      |
| 1                                                                         | Does the health center's standard operating procedure fulfill the following criteria?                                                                                                                                                                          |                      |
|                                                                           | 1. Newborn infant weighed within 24 hours of birth
AND
2. Use electronic scale which is graduated to 10 grams
AND
3. Scale is calibrated at least once a year      AND
4. Scale placed on level, hard surface      AND
5. Scale tared to zero grams | Yes
No
Unknown |
|                                                                           | 1. Newborn infant weighed within 24 hours of birth
AND
2. Scale (electronic/ spring) is graduated to at least 50 grams      AND
3. Scale is calibrated at least once a year, or more often if moved      AND
4. Scale tared to zero grams or 0.00kg       | Yes
No
Unknown |

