### **Low birth weight**

#### Level 1 of diagnostic certainty

Newborn infant weighed within 24 h of birth

AND

Use electronic scale which is graduated to 10 g

AND

Scale is calibrated at least once a year

AND

Scale placed on level, hard surface

AND

Scale tared to zero grams

AND

Weight recorded as <2500 g

OR

Birth weight recorded as <2500 g

AND

Birth weight assessed as per health care facility's standard operating procedure, which fulfills criteria 1 to 5 of LOC1

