#### Level 3 of diagnostic certainty

Newborn infant weighed on day 1 or 2 of life (first 48 h of life)

AND

Weight measured using dial/spring/color-coded scale

AND

Weight assessed as <2500 g

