#### Level 2A of diagnostic certainty

- Weight below 10th percentile for gestational age
- AND
- The following used in assessment of weight
  - o Newborn weighed within 24 h of birth on any scale with a <50 g resolution, tared to zero and calibrated
 AND
- The following for assessment of gestational age:
  - o Certain LMP with first or second trimester ultrasound
 OR
  - o Certain LMP with first trimester physical exam^3

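### The weighing-time answers on the birth weight form overlap, so at a site without a qualifying weighing SOP a day-1 electronic-scale weight can be recorded truthfully and still meet no low-birth-weight level

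*Protocol*

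**What the plan says.** The birth weight reference form in Annex V serves low birth weight, small for gestational age (SGA) and neonatal death. Its item B5 gives four answers on weighing time: "Within 24 hours of birth", "On day 1 or 2 of life (first 48 hours", day 3 or later, and unknown.

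Annex III sets these conditions for low birth weight:

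- **Level 1, direct criteria:** "Newborn infant weighed within 24 h of birth", together with "Use electronic scale which is graduated to 10 g" and conditions on calibration, surface and taring.
- **Level 2, direct criteria:** the same 24-hour window, on an electronic or spring scale (colour-coded included) graduated to at least 50 g.
- **Level 3:** the first 48 hours, with "Weight measured using dial/spring/color-coded scale".
- **Level 4:** the first 48 hours, with a proxy measure.

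Levels 1 and 2 each have an alternative route through the facility's procedures. For Level 1 it reads "Birth weight assessed as per health care facility's standard operating procedure, which fulfills criteria 1 to 5 of LOC1". The birth weight form records the SOP status once per site as yes, no or unknown.

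For SGA, Level 1 also needs weighing within 24 hours, and Levels 2A and 2B need "Newborn weighed within 24 h of birth on any scale" meeting resolution, taring and calibration conditions. Level 3A accepts the first 48 hours. SGA has no SOP route.

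**The concern.** For any infant weighed in the first 24 hours, two answers to B5 are true. The levels treat those answers differently, so the classification can depend on which correct box was ticked.

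Nothing else shown in the protocol would catch this. Classification is automated (section 4.10). Data are analysed as recorded, without imputation (section 5.5). A case that meets no level stays in the applicability denominator as long as its form was completed (section 5.2.2.1). Range and logic checks cannot flag an answer that is true, and the birth weight form holds no date or clock time of weighing.

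The results exposed are applicability (primary outcome 2) and the distribution over levels (secondary outcome 1), for low birth weight and SGA. Type of scale is also one of the equipment factors examined in section 5.3.2, and electronic is the only scale type for which this overlap can remove a low-birth-weight case from classification altogether.

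**Working it through.** **1. Low birth weight, rule by rule.** Take a recorded weight under 2500 g, no proxy, and a scale that is calibrated, tared and on a level surface, weighed on day 1. Applying Annex III gives:

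| Scale | B5 = within 24 h, no qualifying SOP | B5 = first 48 h, no qualifying SOP | B5 = first 48 h, qualifying SOP |
|---|---|---|---|
| Electronic, 10 g | Level 1 | none | Level 1 or 2 |
| Electronic, 50 g | Level 2 | none | Level 1 or 2 |
| Spring or colour-coded | Level 2 | Level 3 | Level 1 or 2 |
| Dial | Level 3 | Level 3 | Level 1 or 2 |

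In the last column the level is 1 if the SOP meets the Level 1 list and 2 if it meets only the Level 2 list. The empty cells need three things together: the 48-hour answer, an electronic scale, and no qualifying or known SOP.

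An infant truly weighed between 24 and 48 hours on an electronic scale at such a site also meets no level. That follows from the definition, not from the form. The difficulty is that B5 cannot tell this infant from one weighed at 2 hours and given the wider answer.

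**2. SGA.** The 48-hour answer removes Levels 1, 2A and 2B. Level 3A then accepts any tared, calibrated scale with resolution under 50 g, electronic included, but has its own gestational-age criteria. With a certain last menstrual period (LMP) and a recorded birth weight, 3A is met. With an uncertain LMP and a second-trimester scan (the Level 2B case), 3A needs a first-trimester physical examination. The gestational age form ends once that scan is documented, so the examination item is never reached. Level 3B requires weighing by difference with an adult, and Level 4 does not describe this infant. Read literally, such a case has no level.

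**3. Size.** The nearest planned figure is the precision target in section 5.1.2, Table 1. With n = 1.96² × p(1 − p)/d², p = 0.5 and d = 0.10, n = 96.04, rounded up to the stated 97. At the target of 100 cases the half-width is 1.96 × √(0.25/100) = 0.098, or 9.8 points.

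If k of N otherwise classifiable low-birth-weight cases at a site without a qualifying SOP are lost this way, applicability falls by 100k/N points. The documents give no k, so these values are assumptions for N = 100:

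- k = 1: 1 point
- k = 5: 5 points
- k = 10: 10 points, about the planned half-width
- k = 20: 20 points

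This is a bias, so recruiting more cases does not reduce it.

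**The case against.** The answers run from narrow to wide in wording close to the definitions, and the narrow one comes first. Trained staff would naturally choose it for an infant weighed at 2 hours. The protocol provides for a manual of study procedures (section 4.9), eCRF completion guidelines (section 8.2) and training on the forms (section 8.7). These are not shown and may contain a rule for B5. This stands as an argument that the frequency may be low. It does not make the printed answers exclusive.

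The SOP route also protects low birth weight at every qualifying site. This stands too, and it confines complete loss of classification to sites whose SOP answer is no or unknown.

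A reader might infer several stronger things that the documents do not support:

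- **That better-equipped sites will look worse.** Such sites may well be the ones whose SOP qualifies, and the documents do not show otherwise.
- **That SGA fails in the same way.** Level 3A admits electronic scales, so many SGA cases would only drop a level. Whether a case is lost turns on gestational-age evidence, not on scale type.
- **That the calibration answers cause the same harm.** "At least once a year, or more often if moved" and plain annual calibration both satisfy the annual criterion of Level 1.
- **That the graduation answers do equal damage.** A 10 g scale can also be read as graduated to at least 50 g, but for low birth weight this costs at most Level 1 to Level 2.
- **That applicability falls by a stated percentage.** Neither the miscoding rate nor a baseline applicability is given, and a proportional fall would hold only if every classified weight were a day-1 electronic one.

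**Conclusion.** The point holds in a limited form. The overlap in B5 is literal, and Annex III makes the choice matter. At a site without a qualifying or known weighing SOP, a day-1 electronic-scale weight recorded under the 48-hour answer meets no low-birth-weight level, although the same infant would be Level 1 or 2 under the other answer. Spring and colour-coded weights fall to Level 3. SGA loses Levels 1 to 2B and keeps 3A only where its gestational-age criteria are met.

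The effect is 1 percentage point of site applicability per 1 in 100 low-birth-weight cases so recorded. The total is unknown, because neither the rate of such recording nor the number of sites without a qualifying SOP is in the protocol. The conclusion assumes that B5 is the only weighing-time input to the classification and that no unseen instruction settles the choice. The correction is worth making because it is cheap and removes a source of bias from a primary outcome.

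**What to change.** Replace the B5 answers with exclusive ones: within 24 h; more than 24 h and up to 48 h; more than 48 h; unknown.

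For forms already completed, the old 24-hour answer carries over directly and the old day-3 answer maps to more than 48 h. Query the 48-hour records against source when the scale is electronic, and for all SGA cases. A date-based recode helps only in part. The only weighing date is item 13d of the gestational age form, which the low-birth-weight form does not call and which is skipped after an informative first- or second-trimester scan. Where 13d was recorded and equals the date of birth, recode to within 24 h; otherwise query.

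As a minor addition, make the graduation answers exclusive, with cut-points that serve both definitions: 10 g or finer; coarser than 10 g but under 50 g; exactly 50 g; coarser than 50 g; unknown. Exactly 50 g needs its own answer because Levels 2A to 3A of SGA require resolution under 50 g, whereas Level 2 of low birth weight accepts 50 g. The calibration item needs no change.

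The cost is an edit to one or two answer lists in the data capture system and a set of queries. Version 3.0 is dated November 2019 and section 10 plans case identification from May 2019, so the edit would fall mid-study and the mapping from old to new codes must be documented. If the edit is judged to affect procedures, section 8.8 requires ethics approval first.
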